## Abstract

**Background:**

During the past decade an increasing number of people live with advanced cancer mainly due to improved medical treatment. Research has shown that many people with advanced cancer have problems with everyday activities, which have negative impact on their quality of life, and that they spend a considerable part of their time at home. Still, research on interventions to support the performance of and participation in everyday activities is only scarcely available. Therefore, the occupational therapy-based “Cancer Home-Life Intervention” consisting of tailored adaptive interventions applied in the participant’s home environment was developed.

The objective of this study is to examine the effectiveness and cost-effectiveness of the Cancer Home-Life Intervention compared to usual care on the performance of and participation in everyday activities and quality of life in people with advanced cancer living at home.

**Methods:**

The study is a randomised, controlled trial (RCT) including an economic evaluation. The required sample size of 272 adults living at home will be recruited from outpatient clinics at two Danish hospitals. They should be diagnosed with cancer; evaluated incurable by the responsible oncologist; and with a functional level 1–2 on the WHO performance scale. The primary outcome is the quality of performance of activities of daily living. Secondary outcomes are problems with prioritised everyday activities; autonomy and participation; and health-related quality of life. Participants are randomly assigned to: a) The Cancer Home-Life Intervention in addition to usual care, and b) Usual care alone.

**Discussion:**

The trial will show whether the Cancer Home-Life Intervention provides better support for people with advanced cancer living at home in performing and participating in everyday activities, and whether it contributes to their health-related quality of life. The economic evaluation alongside the RCT will show if the Cancer Home-Life Intervention is cost-effective. The trial will also show the acceptability of the intervention to the target group, and whether subgroups of participants will benefit more than others.

**Trial registration:**

ClinicalTrials.gov Identifier NCT02356627. Registered 02/02/2015.

## Background

The number of people living with advanced cancer is increasing [1], and it is estimated that the majority of these people are in need of palliative care [2, 3]. According to the World Health Organization (WHO), some of the goals of palliative care are to alleviate adverse consequences of the disease, to improve the quality of life, and to help patients with life-threatening illness to live as actively as possible [4]. Advanced cancer, defined as cancer diagnosed as incurable by the responsible oncologist, can cause functional limitations [5, 6], which may result in decreased ability and energy to perform everyday activities, such as self-care, household, leisure and work [7–9]. A recent study found that 48 % of patients with advanced cancer (*N* = 977) had problems with everyday activities, and that 29 % had unmet needs regarding these [2]. In another study, more than 43 % of women with metastatic breast cancer (*N* = 163) had difficulties with activities of daily living (ADL) and 74 % with instrumental activities of daily living (IADL) [10]. Further, in a study of people with advanced cancer, 10-30 % reported that they had needs in performing everyday activities, i.e. activities that, in addition to ADL and IADL, include leisure and work [11]. Consequently, many people with advanced cancer are not able to perform needed and desired everyday activities, which may lead to reduced quality of life for the individual [12, 13].

Despite the knowledge about the problems and needs of people with advanced cancer related to everyday activities, palliative care rarely encompasses interventions that focus on enabling everyday activities [14–16], and little is known about how the everyday activities are specifically affected and what kind of support is needed. Prior to the present study, a cross-sectional study was conducted to delineate the everyday activity problems, particularly in regard to ADL performance, activities prioritised to be solved, and intervention needs [17–19]. In all, 164 participants with an advanced cancer, a mean age of 67 years, and a WHO Performance Status of 1–3 were included. The findings showed that many participants had functional limitations such as fatigue and pain, and that their ADL performance was characterised by increased effort and reduced efficiency, safety and independency. About half had ADL motor ability below age expectations. The ADLs that caused most problems were physically demanding activities such as cleaning, laundering, and cooking, while fewer problems with self-care were found [18]. The study showed that the everyday activities which the participants had problems with and prioritised being solved mostly concerned leisure, social and domestic activities, along with a wish for improved mobility, autonomy and participation [18].

A Danish randomised controlled trial (RCT) demonstrated that an activity-focused hospital-based intervention was feasible for people with advanced cancer [20]. The study did not identify superior effect of the intervention partly due to a small sample size [21]. A systematic review has indicated that home-based interventions can improve health-related quality of life and satisfaction with palliative care, reduce depressive symptoms, societal costs, and the number of hospital admissions [22]. In addition, a study has shown that people with advanced cancer spend a considerable part of their time at home [23]. Hence a home-based intervention may be more appropriate than a hospital-based intervention in order to enable everyday activities for people with advanced cancer.

We only identified one home-based intervention study aimed at supporting everyday activities for people with cancer. Hegel et al. performed a pilot RCT of a telephone-delivered problem-solving occupational therapy intervention lasting less than a mean time of 106 min. They found that participation restrictions in everyday activities among rural breast cancer patients undergoing chemotherapy seemed to be decreased due to the intervention [24]. When searching for interventions for groups with activity problems similar to those of people with advanced cancer, such as people with chronic diseases and older people with functional limitations, we only identified few studies. The interventions mainly consisted of adaptation of everyday activities, energy conservation, provision of assistive or mainstream technologies, and home modifications, resulting in improved functioning in everyday activities and quality of life [25–29].

Based on the cross-sectional study, existing studies and available guidelines, a literature review, and consultation with representatives of the target group, the “Cancer Home-Life Intervention” was developed and pilot-tested. The intervention applies adaptive strategies, defined as individual plans to overcome particular challenges or to meet the needs of the study participants [30, 31], and aims to compensate for functional limitations, enhance participation in everyday activities, and support resource/energy preserving activity patterns of people with advanced cancer. The intervention has undergone a small feasibility trial (*N* = 4) showing that the intervention was acceptable for the study participants and possible to implement. Since the Cancer Home-Life Intervention is newly developed an evaluation of its effectiveness and cost-effectiveness is required prior to wider implementation. This study protocol outlines how we intend to conduct such evaluation.

## Study objective

The overall objective of this study is to examine the effectiveness and cost-effectiveness of the Cancer Home-Life Intervention compared to usual care on the performance of and participation in everyday activities and health-related quality of life in people with advanced cancer living at home.

### Specific aims

To examine the effectiveness of the Cancer Home-Life Intervention in terms of quality of ADL performance as a primary aim and in terms of problems with everyday activities prioritised to be solved; autonomy and participation in the dwelling; and health-related quality of life as secondary aims.To investigate whether the Cancer Home-Life Intervention is especially effective in some subgroups of people with advanced cancer defined by age, gender, primary cancer diagnosis, and the WHO Performance score.To explore how people with advanced cancer experience the usefulness of the intervention, and how activity patterns change over time in the two groups.To investigate the cost-effectiveness of the Cancer Home-Life Intervention.

#### Hypotheses

The quality of ADL performance as demonstrated by motor and process ability will be better in participants undergoing the Cancer Home-Life Intervention compared to participants who receive usual care.Participants undergoing the Cancer Home-Life Intervention will report less difficulty with prioritised everyday activities, better autonomy and participation, and higher levels of health-related quality of life compared to participants who receive usual care.The Cancer Home-Life intervention provides more Quality Adjusted Life Years (QALYs) at a higher incremental cost.The Cancer Home-Life intervention is cost-effective in a health sector perspective.

## Methods

### Trial design

The study is designed as a RCT using a combination of quantitative and qualitative methods. A health economic evaluation will be performed alongside the RCT.

### Enrolment procedure

At each participating hospital, nurses, secretaries, or the Palliative Team will screen all potential participants for inclusion in the study during 24 months. When eligible participants are identified, the contact information is given to a P-OT responsible for enrolment of study participants. The P-OT will contact all potential participants and provide detailed verbal and written information about the study. Prior to inclusion, the study participants are to give written permission.

## Intervention and control

### Intervention

The Cancer Home-Life Intervention is described in a detailed intervention manual (unpublished, can be retrieved from the authors) and is provided by trained Intervention Occupational Therapists (I-OT). The intervention program is occupational therapy-based and encompasses individually tailored combinations of the following elements: 1) prioritisation of resources, energy, and everyday activities; 2) adaptation of activities; 3) adaptation of posture and seating positioning; 4) provision of assistive devices; 5) modification of the physical home environment. Intervention elements are selected in co-operation between the participant and the I-OT by means of an interview with the participant based on the individual’s problems and needs. The intervention is provided through instruction in and training of the selected strategies, such as how to conduct activities in energy conserving and strain minimizing ways, and guidance and training in safe and efficient use of assistive devices. It is provided in the participant’s home within a week after baseline data collection and completed within three weeks after the initial home visit. The intervention will encompass 1–3 home visits followed by 1–3 telephone calls. When needed, the participant can also contact the I-OT.

In addition to the Cancer Home-Life Intervention, the participants in the intervention group will receive usual care as offered by the hospital and municipality. Usual care aimed at enhancing everyday activities of people with advanced cancer sometimes consists of provision of assistive devices and home modifications, but not necessarily provided systematically. All participants will be allowed to use available medical services such as rehabilitation and palliative care.

Four I-OTs, two at each hospital, will provide the intervention after having attended a one-day training course in the application of the Cancer Home-Life Intervention. Regular meetings will be held with the I-OTs in order to ensure that the intervention is applied according to the manual and as similar as possible across hospitals. The I-OTs will document adherence to the intervention manual by registering which components of the Cancer Home-Life Intervention they have provided to each participant. The study participants will register in a structured questionnaire which everyday activity enabling interventions they have been offered and report whether they have used them.

### Control

Participants in the control group will receive usual care as offered by the hospital and municipality, described above.

## Instrumentation

### Primary outcome

Quality of ADL performance is measured by *The Assessment of Motor and Process Skills (AMPS)* [33]. The AMPS is a standardised, observation-based assessment designed to evaluate the quality of a person’s ADL performance regarding ease, efficiency, safety, and independence. A trained and calibrated P-OT observes the quality of 16 motor and 20 process performance skills (ADL ability) while the person performs two familiar and relevant ADLs, and rates the person’s performance of each skill on a four-point ordinal scale. The ADL motor ability is a measure of how much physical effort, clumsiness, and/or fatigue the person demonstrates during ADL performance. The ADL process ability is the person’s overall efficiency regarding appropriate use of time, space, and objects throughout ADL performance. The ordinal scores are converted into two overall linear ability measures by Rasch-based computer-scoring software: one for ADL motor ability and one for ADL process ability expressed in logistically transformed probability units (logits). The two overall linear ability measures are adjusted for task challenge, skill item difficulty, and rater severity. ADL motor ability above 2.0 logits and ADL process ability above 1.0 logits indicate competent ADL performance, and 0.3 logits a clinical relevant change [33]. In the present study, the ADL motor ability is used as the primary outcome. The P-OT also assesses the five most effective and the five most ineffective ADL motor and process skills based on clinical reasoning [33]. The AMPS has been found valid and reliable in people with advanced cancer [34, 35] and responsive in people with other disorders [33].

### Secondary outcomes

#### Problems with everyday activities prioritised to be solved

Problems with everyday activities at home that the participants face and prioritise to have solved, will be assessed using the *Individually Prioritised Problems Assessment (IPPA)* [36]. The instrument has a structured interview format where the participant identifies up to seven everyday activity problems and rates the importance of and ease/difficulty with each of these problems on five-point ordinal scales from 1 to 5, where 1 = not important at all and 5 = most important; and 1 = no difficulty at all and 5 = too much difficulty to perform the activity at all. The importance scores and the difficulty scores of each activity are multiplied. The scores are then added up and divided by the number of activity problems, resulting in an average IPPA score between 1 and 25. Higher average IPPA scores indicate more difficulty with the prioritised everyday activities [36]. The IPPA has been found to be a useful, responsive, and valid instrument in older people who use assistive devices [37, 38].

#### Autonomy and participation in the dwelling

Autonomy and participation are assessed using three subscales of the Danish version (IPA-DK) of the *Impact on Participation and Autonomy Questionnaire (IPAQ)* [39, 40]. The IPA-DK is a questionnaire targeting adults with chronic functional limitations. It assesses person-perceived participation restrictions via 32 items organised into five subscales: 1. Autonomy indoors, 2. Family roles, 3. Autonomy outdoors, 4. Social life and relationships, and 5. Work and education. For this study, the subscales 1, 2, and 4 are used. Response options are given on five-point ordinal scales from 0 = very good to 4 = very poor. In addition, there are nine items which quantify the degree to which the respondents perceive these restrictions as problematic in their daily life. As these are used for clinical decision making, they are not included in this study. IPAQ is available in several language versions which have well-documented psychometric properties, and the Danish version has undergone a reliability test with satisfactory results [39].

#### Health-related quality of life

Health-related quality of life will be assessed by means of *The European Organization for Research Treatment of Cancer Quality of Life Questionnaire Core 30 (EORTC QLQ C-30)* [41], designed to assess the health-related quality of life of persons with cancer. The instrument consists of nine scales assessing: physical function, role function, emotional function, cognitive function, social functioning, global health status/quality of life, fatigue, nausea and vomiting, and pain, and six single-item scales: dyspnoea, insomnia, lack of appetite, constipation, diarrhoea, and financial difficulties. All the scales and single-item measures range in a score from 0 to 100. Higher score represents a higher (“better”) level of functioning or a higher (“worse”) level of symptoms [41]. The EORTC QLQ C-30 is a well-validated and reliable instrument within cancer research [42, 43]. Additionally, health-related quality of life will be measured by the use of the *EuroQol instrument (EQ-5D-5L)* [44]. The EQ-5D-5L is a generic instrument measuring health-related quality of life, and it is widely used in economic evaluations. The instrument consists of five dimensions: mobility, self-care, usual activities, pain/discomfort and anxiety/depression. The participant scores each dimension on a five-point ordinal scale ranging from no problems to severe/extreme problems. A Danish set of preference values was constructed based on interviews with 1332 Danish respondents [45]. The psychometric properties of the EQ-5D-5L including the Danish version have been extensively investigated and are considered as good [46]. The data from the EQ-5D-5L will be used for the economic evaluation alongside the RCT.

### Descriptive data

#### Everyday activity pattern

The everyday activities that the participants engage in during a day will be captured by the Time Geographical method using a semi-structured diary [47]. The participants will be required to record the activities they undertake during one day of their own choice. The diary encompasses domains regarding which activities the participants engage in during the day, at what time, for how long, whom they are with, where they are, and how they feel physically and mentally [47].

#### Joyful activities

As a way to better understand what activities are of importance to the participants they are asked which everyday activities they regard as especially joyful [48].

#### Experienced usefulness

Participant observations will be conducted during 10–20 intervention sessions depending on the number of interventions provided for the individual participants [49]. In addition, telephone interventions provided to this sub-sample will be electronically recorded. In particular, attention will be on the participants’ reactions to the intervention as it takes place.

Qualitative interviews will be conducted in conjunction with data collection at follow-up in the participants’ homes. The interviews that will explore the usefulness of the intervention will be based on an interview guide developed from a preliminary analysis of the previous participant observations to acquire the participants’ experiences of the intervention received and its usefulness.

### Cost data

#### Intervention costs

The intervention costs will be measured based on micro costing including occupational therapists’ and study participants’ time spent on the intervention; the costs for applications and assistive devices and home modifications; the occupational therapists’ time used for related administrative purposes and transportation.

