#### Costs in the secondary health care sector

The costs of secondary health care will be determined by Diagnostic Related Group (DRG) tariffs extracted from the National Patient Registry (NPR). The data include information on hospital departments, dates of admission and discharge, and diagnosis [50].

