#### Costs in the primary health care sector

Data on the use of primary health care including contacts to general practitioners, medical specialists, and physiotherapists will be extracted from The Danish National Health Service Register for Primary Care (NHSR) and valued using the activity-based fees that are used to reimburse these providers. The NHSR contains information about the activities of health professionals’ contacts with the tax-funded public health care system [50].

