#### Study participants’ out-of-pocket costs

Out-of-pocket costs such as non-prescriptive medication, dietary supplements, informal care, aids, and short term sick leave are assessed using a modified version of the Dutch cost diary [51]. The patient out-of-pocket costs will solely be included in the sensitivity analysis.

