### Data analysis for the economic evaluation

The economic evaluation will be conducted as a cost-effectiveness analysis. A health sector viewpoint will be taken to estimate the costs of all activities and resource use related to the study participants’ disease. T1 will be taken as the start of the time frame that will end at T4. All costs will be reported in 2015-Euros. By the use of register data to estimate costs, we expect a full follow-up of these data. The method of multiple imputation [58] will be used to handle possible lost to follow-up in the ADL motor ability or the EQ-5D-5L due to other reasons than death.

In the cost-effectiveness analysis the ADL motor ability will be used as the clinical parameter and QALY will be used as the measure of utility. In order to calculate QALY the EQ-5D-5L the recommended standard mapping procedure will be used based on the Danish preference weights [45]. The QALYs over 24 weeks will be calculated by interpolation of the area under the curve with four time points (T1, T2, T3, and T4). The resource use, costs, and clinical outcome will be presented as means with 95 % bootstrapped confidence intervals (10,000 replicates) [62]. The Incremental Cost-Effectiveness Ratio (ICER) will be calculated using the formula: ICER = (C_A_ – C_B_) / (E_A_ – E_B_), where C denotes costs and E denotes effects with A and B referring to comparators. The ICER summarises the results of each economic evaluation in a single parameter, defined as the ratio of additional costs per additional unit of effect [53]. The ICER is, however, undefined if the ratio or just one of the confidence limits is negative.

The result of the cost-effectiveness analysis will be summarised in cost-effectiveness acceptability curves (CEAC) [63]. A CEAC is a graphic representation of the uncertainty in cost differences and effect differences between the two groups [63]. To deal with the structural uncertainties, sensitivity analysis will be performed to test the influence of the chosen imputation strategy. Further sensitivity analysis will be performed to test the inclusion of productivity costs and patients’ out-of-pocket payments [53].

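### Base-case costing departs from the stated health sector viewpoint and is not symmetric between arms: participants' time is included, while usual-care devices and home modifications have no named category

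*Protocol article*

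**What the plan says.** All references are to the protocol article.

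- **Viewpoint.** Data analysis for the economic evaluation: "A health sector viewpoint will be taken to estimate the costs of all activities and resource use related to the study" participants' disease, from baseline (T1) to week 24 (T4). Hypothesis 4 is also framed in a health sector perspective.
- **Intervention costs.** Micro-costing covers therapists' and participants' "time spent on the intervention; the costs for applications and assistive devices and home modifications", plus therapists' administration and transport. Nothing restricts any of these items to a sensitivity analysis.
- **Other cost categories.** For hospital care, "The costs of secondary health care will be determined by Diagnostic Related Group (DRG) tariffs". For primary care, "contacts to general practitioners, medical specialists, and physiotherapists will be extracted" from a register. Redeemed prescriptions come from a third register.
- **Sensitivity analysis only.** "The patient out-of-pocket costs will solely be included in the sensitivity analysis"; these include informal care, aids and short-term sick leave. Productivity costs are treated in the same way.
- **Usual care.** Under Intervention, usual care directed at everyday activities "sometimes consists of provision of assistive devices and home modifications, but not necessarily provided systematically". It is given in both arms: "the participants in the intervention group will receive usual care as offered by the hospital and municipality", and "Participants in the control group will receive usual care as offered by the hospital and municipality, described above".

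**The concern.** Two separate features of the base case do not fit the declared viewpoint.

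First, participants' time is borne by the participant, not by the health sector. Only the intervention arm can spend time on the intervention, so the item enters one side of the cost difference.

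Second, assistive devices and home modifications are two of the five intervention elements and are micro-costed as such. When hospital or municipality supplies the same items as usual care, no base-case category names them. Whether an item is costed then depends on who handed it over. If a participant receives from the trial therapist something the municipality would otherwise have supplied, the intervention is charged for it and the saving is not credited.

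Both features act on the numerator of the incremental cost-effectiveness ratio. They therefore bear on Hypothesis 3, which predicts a higher incremental cost, and on Hypothesis 4, which claims cost-effectiveness for the health sector.

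**Working it through.** The article states no cost figure, so there is none to reproduce. The check consists of placing each resource in the cost categories and then doing the algebra of the cost difference.

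**Step 1: where each resource falls**

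| Resource | Base case | Sensitivity analysis |
|---|---|---|
| Therapist time, administration, transport | Yes (Intervention costs) | – |
| Participants' time on the intervention | Yes, as written (Intervention costs) | Not listed |
| Devices and modifications supplied by the intervention | Yes (Intervention costs) | – |
| Devices and modifications supplied as usual care | No category names them | Not listed |
| Aids bought by the participant | No | Yes (out-of-pocket) |
| Informal care, short-term sick leave | No | Yes (out-of-pocket) |
| Productivity costs | No | Yes |

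**Step 2: error in incremental cost**

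Per participant, let:
- D = mean cost of devices and modifications supplied by the intervention;
- U = mean cost of usual-care devices and modifications in the control arm;
- s = share of U that the intervention displaces, so the intervention arm still receives (1 − s)U from usual care;
- tau = value placed on participants' time;
- R_A and R_B = all remaining base-case costs in the intervention and control arms.

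As planned: C_A − C_B = (D + tau + R_A) − R_B.

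Symmetric, health sector only: C_A − C_B = (D + (1 − s)U + R_A) − (U + R_B) = D − sU + R_A − R_B.

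Planned minus symmetric = **s × U + tau**.

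**Step 3: range**

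The article gives no unit costs, no frequency of usual-care provision and no value of time. As assumptions, in units of D, take U from 0.1 to 0.5 and tau from 0 to 0.3. The device term s × U is then:

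| s | U = 0.1 | U = 0.3 | U = 0.5 |
|---|---|---|---|
| −0.5 (intervention prompts extra municipal provision) | −0.05 | −0.15 | −0.25 |
| 0 (purely additive) | 0 | 0 | 0 |
| 0.5 | +0.05 | +0.15 | +0.25 |
| 1 (full displacement) | +0.10 | +0.30 | +0.50 |

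The time term adds 0 to +0.3 to every cell. For example, s = 0.5, U = 0.3 and tau = 0.1 give 0.5 × 0.3 + 0.1 = +0.25 of D. Over the whole grid the total runs from −0.25 to 0.50 + 0.30 = +0.80. The time term is never negative; the device term can take either sign.

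**Step 4: what is already collected**

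Under Data collection, the T2 (week 6) questionnaire asks both groups which interventions they received. A device-use questionnaire is filled in at T1 and again at T3 (week 12), since T3 repeats T1. The T4 questionnaire holds only the cost diary and the EQ-5D-5L. Nowhere does the article say that the T2 or device-use data will be priced for usual care.

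**The case against.** - **Cancellation.** The intervention arm also receives usual care, so usual-care items left out of both arms cancel unless the intervention changes their provision. This stands. A reader might infer that the omission necessarily inflates incremental cost, or that the error equals the whole mean device cost in the control arm. The documents support neither: the first needs s > 0 and the second needs s = 1.
- **Table 1.** It gives a questionnaire at week 6 as the source for intervention costs, and the week-6 questionnaire on interventions received covers both groups. Usual-care items might therefore be meant to be costed from it. This leaves some ambiguity, as does the promise to cost all disease-related resource use. However, the cost section ties the category to the intervention, and no sentence extends it to usual care. A week-6 entry would also leave the rest of the 24-week time frame uncovered.
- **Condensed article.** Unit prices and the costing template may properly sit in a fuller document, and their absence is no fault. The point rests on what the article does state: its list of cost categories and its viewpoint.
- **Patient costs.** A reader might infer a general rule that all patient costs belong in the sensitivity analysis. The article has none; it confines out-of-pocket and productivity costs, and time on the intervention is in neither list. What remains is the conflict between counting that time and declaring a health sector viewpoint. The amount may be modest, since contact is one to three visits and one to three calls.

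**Conclusion.** The point holds in two parts of different strength.

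1. **Participants' time.** As written, the base case includes a cost outside the declared viewpoint, in one arm only. The error is tau: upward for any positive valuation and zero only if the time is measured but not valued. It rests on reading intervention costs as base-case costs, which follows because only out-of-pocket and productivity costs are set aside for sensitivity analysis.
2. **Devices and home modifications.** The costing is asymmetric by supplier. The resulting error is s × U. Upward is the likelier direction, because someone equipped by the trial therapist has less need of the same item from the municipality. That is a judgement, and the article offers no data on displacement or on how often usual care provides these items. The error is zero without displacement and negative if the intervention triggers further municipal provision.

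No euro amount can be derived from the article; the ranges above are assumptions. The matter affects incremental cost and the ratios built on it, not the clinical comparison.

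**What to change.** - Move participants' time to the sensitivity analysis, alongside out-of-pocket and productivity costs. Alternatively, keep it in the base case and change the stated viewpoint to one that includes participant-borne costs.
- State that assistive devices and home modifications are costed in the base case for both arms, whoever provides them, with one common set of unit prices. Use the T2 questionnaire on interventions received and the device-use questionnaire at T1 and T3.
- Say how items supplied between week 12 and week 24 are handled. No source is named for them, so either add a question at T4 or declare the gap as a limitation.

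The cost is a change of wording and some extra unit-cost work. The T1–T3 questionnaires are already planned in both groups, so no new visit is needed. The downside is reliance on self-report for usual-care items, in contrast with the register sources used for the other health-sector costs.
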